**Methods:**

This is a non-inferiority cluster-randomized trial set in Dar es Salaam, Tanzania. A cluster is one of 48 healthcare facilities with its surrounding catchment area. 24 clusters were randomized to ART home delivery and 24 to the standard of care. The intervention consists of home visits by CHWs to provide counseling and deliver ART to patients who are stable on ART, while the control is the standard of care (facility-based ART and CHW home visits without ART home delivery). In addition, half of the healthcare facilities in each study arm were randomized to standard counseling during home visits (covering family planning, prevention of HIV transmission, and ART adherence), and half to standard plus nutrition counseling (covering food production and dietary advice). The non-inferiority design applies to the endpoints of the ART home delivery trial; the primary endpoint is the proportion of ART patients at a healthcare facility who are virally suppressed at the end of the study period. The margin of non-inferiority for this primary endpoint was set at nine percentage points.

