17. Ununio	Standard + nutrition	Dispensary	Kinondoni	115	6
18. Mnazi Mmoja Health Centre	Standard + nutrition	Health Centre	Ilala	3,650	4
19. Chanika	Standard	Health Centre	Ilala	1,413	12
20. Segerea	Standard	Health Centre	Ilala	678	8
21. Kiwalani	Standard + nutrition	Dispensary	Ilala	519	13
22. Gerezani	Standard	Dispensary	Ilala	350	2
23. Majohe	Standard + nutrition	Dispensary	Ilala	220	10
24. Mvuti	Standard + nutrition	Dispensary	Ilala	185	16
		Total:		37,977^b^	168

*Abbreviations*: *ART* antiretroviral therapy, *No*. number, *CHW* community health worker

^a^ Half of the clusters in each study arm were randomized to standard counseling and half to standard plus nutrition counseling.

^b^ This is *not* the expected number of participants as many ART patients do not live in the cluster (i.e., in the area surrounding the healthcare facility), and are therefore not eligible for this trial

For the purposes of randomization, clusters were first matched into pairs, separately within each municipality, based on the number of patients currently on ART at the facility. More specifically, the facility with the highest number of ART patients in Temeke was paired with the facility with the second highest number of ART patients in Temeke, and so on. The reason for this choice was that the intervention becomes more complex and thus plausibly less feasible to implement with an increasing volume of eligible participants. Most facilities only have one community outreach nurse. Thus, with an increasing number of eligible participants (for which ART patient volume is a proxy), the number of patients for whom the community outreach nurse has to supervise ART home delivery increases. An added benefit of matching on size prior to randomization is that it ensured an approximately equal number of participants in each study arm. The same process of matching facilities into pairs based on ART patient volume was used to randomize half of the facilities in each study arm to standard counseling and half to standard plus nutrition counseling (Fig. 1). The study design is thus a matched-pair cluster-randomized controlled 2x2 factorial trial. The randomization was conducted prior to the start of the study using computer-generated random numbers. For feasibility reasons, neither the research team nor the study participants are blinded to the intervention assignment.

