### Sample size

Over the enrolment period, we expect to recruit approximately 700 participants in each of the two trial arms (1,400 participants in total). We calculated the design effect (taking into account clustering of outcomes at the facility-level and varying cluster sizes) for this trial using the ‘clustersampsi’ function in Stata [31]. The design effect was then used to adjust the expected power calculated for a non-inferiority trial under individual randomization, which we determined using the ‘ssi’ function in Stata [32]. Our calculations assumed that 85% of enrolled participants are virally suppressed at baseline as found in a recent cross-sectional study in Dar es Salaam [33]. The margin of non-inferiority was set at nine percentage points. We used a range of intra-cluster correlation coefficients (ICCs) from 0.005 to 0.020. Barnhart et al. calculated ICC values for CD4-cell count measures in Dar es Salaam [34]. The 6-months cumulative incidence for non-adherence to ART (defined as a 50% drop in CD4-count from its peak value and return to pre-ART CD4-count or lower after 168 days on ART or a viral load greater than 10,000 after 168 days on ART) had an ICC value of 0.016 (95% confidence interval: 0.009 to 0.029). We set the probability of a type one statistical error at 0.05 and assumed a correlation coefficient between baseline and endline viral load measurement of 0.5. We find that we are well powered (≥80% power) to detect modest one-sided differences (<9 percentage points) in the proportion of participants who are virally suppressed between the two study arms. Regarding the effect of nutrition counseling on BMI, we are well powered (≥80%) to detect a difference in mean BMI of approximately 1.0 kg/m^2^ or more between the participants in the standard versus the standard plus nutrition counseling arm. This difference is considerably smaller than the difference of 3.1 kg/m^2^ found by Alo et al. between female ART patients randomized to six months of nutrition counseling versus the standard of care in Southeast Nigeria [35]. The trial by Alo et al. is, to the best of our knowledge, the only randomized evaluation to date of the impact of nutrition counseling on BMI in ART patients.

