### Analysis plan

We will analyze the data by intention-to-treat analysis at the patient level in all primary analyses for this trial. The primary endpoint of this trial (i.e., the percentage of participants with a suppressed HIV viral load at the end of the study period) will be assessed by fitting robust clustered log-binomial models. Given the relatively small number of clusters in this trial, we cannot assume that randomization will eliminate confounding despite the matching of clusters described in the study design section. We will, therefore, adjust the analysis for viral load suppression at baseline. As viral load suppression is the outcome variable for the primary endpoint, adjusting for baseline viral load could be considered perfect adjustment for confounders. However, in secondary analyses, we will also adjust for other potentially confounding variables (e.g., participants’ socio-demographic characteristics) as a single baseline measurement may not account for trends in viral load suppression over time. Similarly, in secondary analyses, we will adjust for differing average exposure lengths to ART home delivery at each facility, and conduct subgroup analyses according to whether a participant received ART home delivery and by participants’ exposure length to ART home delivery.

Potential effect modification for any of the endpoints of this trial will be assessed through the likelihood ratio test. If statistically significant effect modification is present, we will present relevant results stratified by the effect modifier. All analyses will be conducted using Stata (Release 13; StataCorp, College Station, TX, USA).

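### The likelihood ratio test named for effect modification ignores clustering when paired with the cluster-robust log-binomial model, so facility-level modifiers of viral suppression will look significant too often

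*Protocol article*

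**What the plan says.** Three statements in the Analysis plan of the protocol article bear on this.

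- Level and model: the plan is for "intention-to-treat analysis at the patient level in all primary analyses", and the primary endpoint "will be assessed by fitting robust clustered log-binomial models".
- Test of effect modification: "Potential effect modification for any of the endpoints of this trial will be assessed through the likelihood ratio test".
- Use of the result: "If statistically significant effect modification is present, we will present relevant results stratified by the effect modifier".

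No effect modifier is named, and no random-effects model appears anywhere in the article. The Randomization section describes a design in which the second factor, nutrition counselling, is also allocated by facility: "The study design is thus a matched-pair cluster-randomized controlled 2x2 factorial trial". The Sample size section recognises clustering: "We used a range of intra-cluster correlation coefficients (ICCs) from 0.005 to 0.020".

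**The concern.** A likelihood ratio test needs a likelihood that describes the data. A log-binomial model with cluster-robust variance is estimated as if all patients were independent, and the robust step then repairs the standard errors only. The maximised likelihood is left as it was, and the likelihood ratio statistic is computed from it. For a contrast between facilities the statistic is therefore inflated by roughly the design effect and no longer follows its chi-square reference.

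The article thus accounts for clustering in its sample size and primary model, and loses that protection when it tests interactions. Because significance decides whether stratified results are shown, a test with the wrong error rate leads to too many stratified presentations that rest on chance. This is a test the article fixes in words, not a detail left to a fuller analysis plan.

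**Working it through.** **Inputs from the article**
- 48 facilities, 24 per arm, each arm split 12/12 by counselling package (Abstract; Table 1).
- 700 participants per arm, 1,400 in total (Sample size). Mean per facility m = 1,400/48 = 29.2.
- Suppression 85%, margin nine percentage points, type I error 0.05, ICC 0.005 to 0.020, and a cited ICC of 0.016 with interval 0.009 to 0.029 (Sample size).

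**Assumption.** The article gives no CV for participants per facility. The range 0 to 1 is used. For scale, sizes proportional to the community health worker counts in Table 1 would give a CV of 0.47.

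**The article's own figure.** No error rate is stated for the effect-modification test. The stated power of at least 80% for non-inferiority can be reproduced. With equal facilities, DE = 1 + (29.2 − 1) × ICC, which is 1.141 at ICC 0.005 and 1.564 at 0.020. Effective sizes per arm are 700/1.141 = 613 and 700/1.564 = 448. The standard errors are √(2 × 0.85 × 0.15/613) = 0.0204 and √(0.255/448) = 0.0239. Power is Φ(0.09/SE − 1.645), or 99.7% and 98.3%. The inputs are being read consistently.

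**Approximate size of the naive test, 1 df.** With DE = 1 + ((1 + CV²)m − 1) × ICC, the true size of a nominal 5% test is about P(χ²₁ > 3.84/DE).

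| ICC | CV 0: DE, size | CV 1: DE, size |
|---|---|---|
| 0.005 | 1.14, 6.7% | 1.29, 8.4% |
| 0.016 | 1.45, 10.4% | 1.92, 15.7% |
| 0.020 | 1.56, 11.7% | 2.15, 18.1% |

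**Simulation.** 48 facilities with the counselling labels of Table 1, beta-binomial outcomes around 0.85, no true interaction, no baseline adjustment, 3,000 runs per cell. Rejection by the log-binomial likelihood ratio test of home delivery by nutrition counselling:

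| ICC | equal sizes | CV 0.47 | CV 0.80 |
|---|---|---|---|
| 0.005 | 6.8% | 6.8% | 8.5% |
| 0.016 | 10.1% | 11.6% | 13.8% |
| 0.020 | 11.6% | 13.3% | 16.0% |

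With ICC near zero the same code gave about 5%, as it should. Separate simulations of the same contrast gave up to 15% at ICC 0.016 and up to 17% at 0.020, slightly below the approximation at CV 1.

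**Other modifiers, same simulation**
- Home delivery by municipality (2 df): 7.0-9.3% at ICC 0.005, 12.4-16.7% at 0.016, 14.3-21.4% at 0.020.
- A patient-level factor such as sex: 4.3-6.1% throughout. That contrast is formed within facilities, so the facility effect largely cancels when the arm effect is common across facilities.
- Facility volume was not simulated. It is a facility-level attribute and the same reasoning applies.

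**Baseline adjustment.** The primary model adjusts for baseline suppression. A simulation at ICC 0.016 with baseline-endline correlation 0.5 (CV 0.5 and 1.0; 1,500 runs) gave 13-15% unadjusted. With adjustment the size was 8-9% if facility differences persist from baseline, and 16-20% if they arise entirely afterwards.

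**After the fix.** A cluster-robust Wald test with a t reference on 44 df (48 facilities less four cells; 20,000 runs) rejected 5.8-7.3% at ICC 0.005, 5.3-7.3% at 0.016 and 5.6-7.4% at 0.020. Most of the inflation goes at the higher ICCs. The remainder comes with unequal facilities, which is why a small-sample correction is needed.

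**The case against.** The strongest reply is that little hangs on this test, and several parts of that reply stand.

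- A reader might infer that a significant interaction makes stratified results replace the overall result. The text does not say so. It promises stratified results and nowhere withdraws the overall analysis. The point concerns subgroup reporting only.
- A reader might extend the point to BMI and the secondary endpoints, since the test is named for all endpoints. The article states a model only for viral suppression. A likelihood ratio test from a random-effects model would be sound for the others, so the criticism does not reach them.
- A reader might think every interaction test is inflated, or that the factorial interpretation rests on this one. No modifier is named, home delivery by nutrition counselling is not listed as a test, and patient-level factors stay near 5%.
- The size is uncertain. The CV is assumed, the cited ICC of 0.016 belongs to a composite of CD4 decline and high viral load rather than to suppression, pair matching could lower the effective ICC, and baseline adjustment moves the figure either way. At ICC 0.005 the excess is modest and the robust test gains little.

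None of this makes the named test fit the named model. Adjustment reduced the inflation in the favourable case but did not remove it.

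**Conclusion.** The point holds for facility-level modifiers of viral suppression. For home delivery by nutrition counselling, unadjusted, the nominal 5% test rejects about 7-8% of the time at ICC 0.005 and about 10-17% at ICC 0.016-0.020. At the cited ICC of 0.016 that is two to three times the intended rate. This rests on reading the robust clustered model as an independence likelihood with corrected standard errors, on a participant CV of 0 to 1, and on no baseline adjustment.

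The consequence is false triggering of stratified reporting. The overall non-inferiority comparison does not use this test and is unchanged. The stated rule gives a wrong error rate and is cheap to correct, but it is not a threat to the trial's main conclusion.

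**What to change.** In the Analysis plan, replace the sentence on the likelihood ratio test for the log-binomial models. State that effect modification of viral suppression is tested with a cluster-robust Wald or score test of the product term, using small-sample degrees of freedom based on the number of facilities. If the likelihood ratio test is to be kept, state the random-effects model whose likelihood it uses.

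Add that the interaction estimate and its confidence interval are reported beside the overall effect. This also closes off the reading that strata take the place of the main result.

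The cost is one or two sentences and a different test command. No new data are needed, and the sample size and primary analysis do not change.

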### Ethical considerations

#### Approvals

The study was approved by the research ethics committee of the National Institutes of Medical Research (NIMR) in Tanzania on July 16^th^ 2015 and received an exemption by the institutional review board of the Harvard T.H. Chan School of Public Health in June 2015. NIMR will be informed immediately of any study protocol amendments and the trial registers (RIDIE and ClinicalTrials.gov) will be updated accordingly.

#### Consent

The data collectors placed at each of the study’s healthcare facilities will obtain written informed consent from all participants at enrolment into the study. To adhere to the intent-to-treat principle, patients who refuse to participate in the study at any time during the study period, including during enrolment, will be asked for consent to complete the study questionnaire, and to take a blood sample and BMI measurement at enrolment and at the end of the study period. The data collectors will also obtain written informed consent from respondents before administering the patient exit questionnaire and the healthcare provider questionnaire.

#### Confidentiality

CHWs were instructed to seek a private space in the participant’s home before providing counseling and delivering ART. In addition, potential participants will be asked about whether they have disclosed their HIV status to other household members during enrolment. CHWs will be informed which participants have not disclosed their HIV status to all other household members and be urged to make an utmost effort to maintain the participant’s privacy during their home visits. Similarly, the patient exit and healthcare provider questionnaire will be administered in a space that maximizes the respondent’s privacy.

#### Access to data

The research team at MDH will have access to the full datasets collected as part of this study at all times during the trial. The MDH team will share de-identified datasets with the investigators at the Harvard T.H. Chan School of Public Health on a regular basis.

#### Dissemination of results

The trial results will be disseminated through personal meetings with policy makers in Dar es Salaam, including the municipal leadership and the Tanzanian Ministry of Health and Social Welfare. In addition, the results will be submitted for publication in a peer-reviewed scientific journal and presented at scientific conferences.

### Trial status

Enrolment into the trial has commenced on February 29^th^ 2016 and is currently ongoing.

## Discussion

Most low- and middle-income countries (LMICs) face a severe shortage of nurses and physicians [1], and distance to the nearest healthcare facility is a key barrier to accessing care in many regions [37–40]. Thus, the potential benefits of shifting care from skilled facility-based health worker cadres to lay community-based healthcare workers are evident. While this trial focuses on HIV care, it will contribute to a growing body of evidence on a broader question that is central to current health systems implementation research: what is the acceptability and feasibility of shifting care from facility-based nurses and physicians to lay healthcare workers based in the community, and what is the effect on patients’ health and economic outcomes? The question of whether drugs for chronic diseases can be safely provided by CHWs is one that is becoming increasingly important as the burden of chronic non-communicable diseases in LMICs grows [41]. The regular dispensing of drugs for chronic diseases may be a good candidate for task-shifting to CHWs for several reasons: 1) the frequency of needing to return to a healthcare facility to pick up medications may be determined by a facility’s drug stocks rather than a need for clinical monitoring by a nurse or physician, 2) there is a considerable cost to patients, both in terms of time lost and out-of-pocket expenditures [30], from having to regularly attend a healthcare facility, and 3) non-retention in care is common in many chronic care settings in LMICs [42].

### Limitations

This study has several limitations. First, there is the possibility of selection bias whereby ART patients in a control cluster may hear about the offer of ART home delivery at intervention facilities. These patients may change their care from a control to an intervention facility in order to receive ART at home. To assess whether this is a likely source of bias, we will ask patients at enrolment where and when they have last received ART and, where applicable, why they have changed healthcare facility. An additional threat to the internal validity of this trial could arise if a substantial portion of participants in the ART home-delivery arm does not return to the facility at the end of the follow-up period for a viral load measurement and administration of the endline questionnaire. If the patients who are lost to follow-up in the ART home-delivery arm have systematically different outcomes (e.g., are less likely to be virally suppressed) than patients who are not lost to follow-up, and this difference or the rate of loss to follow-up varies between the study arms, then this would result in bias. To minimize this potential bias, we will undertake additional efforts to collect viral load and BMI data from participants in the ART home-delivery arm who do not return to the healthcare facility at the end of the follow-up period, including taking blood samples for viral load measurement at participants’ homes. A limitation to the external validity of this trial is that it focuses on home delivery of ART for patients who are stable on ART. home delivery of ART may, however, also be feasible for patients who just initiated ART, or whose WHO clinical stage, CD4-cell count or viral load suggests that they are not stable ART patients. For example, in a sub-analysis in patients who started ART with a low CD4-cell count (<50 cells/μL) as part of the cluster-randomized trial in Uganda described in the introduction, Woodd et al. did not find an increased rate of mortality among those who continued to receive ART at home after ART initiation as compared to those who received standard clinic-based care [43].

In conclusion, this is the first randomized health systems implementation trial investigating the feasibility and effectiveness of CHW-led ART home delivery in urban sub-Saharan Africa. The results of this trial will not only inform ART programs in sub-Saharan Africa but also contribute an important piece of evidence to the ongoing policy debate on task-shifting of chronic care from facility- to community-based healthcare workers.

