#### Nutrition counseling

CHWs provide counseling to all participants in both the intervention and control arms during their home visits. As described in the study design section, half of the clusters in each the intervention and control arm of the trial were randomized to standard counseling, and half to standard plus nutrition counseling. The standard counseling covers family planning, ART adherence, and prevention of HIV transmission. Nutrition counseling covers advice on 1) food production for those with access to a garden or plot of land, 2) a healthy diet for people living with HIV, 3) exercise, and 4) monitoring one’s weight. In addition, participants enrolled in the trial at one of the healthcare facilities randomized to the nutrition counseling intervention receive a pack of seeds (amaranth, cowpea, or pumpkin) at enrolment if they report to have access to a garden or plot of land where they can grow vegetables for their own consumption.

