### Endpoints

The primary endpoint for the ART home delivery intervention is the proportion of enrolled patients with a suppressed HIV viral load at the end of the study period (i.e., when the study exit assessment is performed). A substantial proportion of participants does not have a recent viral load or CD4-cell count at enrolment. As described above, the study team obtains a blood sample from these patients at enrolment and sends it to the public healthcare system’s laboratory for a viral load measurement. Because the delay in receiving the viral load count from the laboratory varies between participants (and thus, the time point at which eligibility for ART home delivery can be assessed at intervention facilities), the length of time for which intervention participants receive ART at home varies between participants at a healthcare facility. Participants in the ART home-delivery intervention receive ART at home for a period varying between one and 11 months, and for an average of six months.

The primary endpoint for the nutrition counseling intervention is the mean BMI of participants who received standard counseling by CHWs versus those who received standard plus nutrition counseling, assessed at the end of the study period. Secondary endpoints of this trial (all assessed at the end of the study period) are: 1) participants’ healthcare expenditures in the last six months, 2) self-reported ART adherence during the last one month, 3) the proportion of patients with access to a plot of land who grow vegetables or fruits for their own consumption, 4) diversity of dietary intake, and 5) the proportion of participants who are anemic.

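### Extra tracing and home blood draws for missed exit assessments are assigned to the home-delivery arm alone, so the two arms' observed viral loads are selected differently

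*Protocol article*

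**What the plan says.** The Endpoints section defines the primary outcome as "the proportion of enrolled patients with a suppressed HIV viral load at the end of the study period". The Analysis plan states: "We will analyze the data by intention-to-treat analysis at the patient level in all primary analyses for this trial".

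The Limitations section raises non-return for the exit viral load as a threat in the home-delivery arm. It gives the condition under which loss does harm: those lost have different outcomes, and "this difference or the rate of loss to follow-up varies between the study arms, then this would result in bias". That condition involves both arms. The remedy names one: "we will undertake additional efforts to collect viral load and BMI data from participants in the ART home-delivery arm who do not return", "including taking blood samples for viral load measurement at participants’ homes".

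The only other text on obtaining outcomes outside routine participation is in the Consent section. Patients who refuse participation at any time "will be asked for consent to complete the study questionnaire, and to take a blood sample and BMI measurement at enrolment" and again at the end of the study. This applies to both arms, but it concerns agreement to be measured. It does not describe going to find someone who failed to come.

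**The concern.** An intention-to-treat comparison of a proportion of enrolled patients needs outcomes to be pursued equally hard in both arms. Here the effort depends on the allocated arm, in a trial that the Randomization section describes as unblinded. Patients who stop attending are plausibly less often suppressed than those who keep attending. If such patients are found and bled in one arm but not in the other, the two sets of observed viral loads differ in make-up even when the treatments perform identically.

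The planned adjustment for baseline suppression cannot remove this, because the selection acts on retention after baseline. Nor can any later analysis recover a viral load that was never drawn. The comparison affected is the primary one, judged against a margin of nine percentage points.

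**Working it through.** **The plan's own figure.** The Sample size section claims at least 80% power with about 700 per arm, 85% suppression, a 9-point margin, type I error 0.05, ICC 0.005 to 0.020 and a baseline-endline correlation of 0.5. Inputs to the check are 24 clusters per arm (mean size 700/24 = 29.2), a design effect of 1 + ((CV² + 1) × 29.2 - 1) × ICC, a variance factor of 1 - 0.5², a true difference of 0 and a one-sided test. At ICC 0.020, power is 99.7% with equal clusters, 98.1% at CV 1.0 and 83.0% at CV 2.2. The last CV is that of the ART volumes in Table 1; the article does not state the CV it used. The claim reproduces and is not in dispute. It says nothing about unequal ascertainment.

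**Inputs to the illustration.**
- From the article: 85% suppression (stated there for baseline) and the 9-point margin.
- Assumed, because the article gives neither: the share d not returning for the exit assessment, and suppression s among them.
- Also assumed: no true difference, d and s the same in both arms, a fraction f of home-delivery non-returners reached, and no control non-returners reached.

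**Formulas** (home delivery minus control, on the difference scale because the margin is stated there):
- Suppression among returners: r = (0.85 - d × s) / (1 - d).
- Missing excluded: [(1 - d) × r + d × f × s] / [(1 - d) + d × f] - r.
- Missing counted as not suppressed: d × f × s.

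**Example: d = 10%, s = 50%, f = 1.**
- r = (0.85 - 0.05) / 0.90 = 0.889.
- Missing excluded: 0.850 - 0.889 = **-3.9 points**.
- Missing as not suppressed: control shows 0.90 × 0.889 = 0.800, so 0.850 - 0.800 = **+5.0 points**.
- With half reached (f = 0.5): 0.825/0.95 - 0.889 = -2.0 points, or 0.825 - 0.800 = +2.5 points.

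**Range with f = 1** (missing excluded / missing as not suppressed, in points):

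| d | s = 40% | s = 50% | s = 60% | s = 70% |
|---|---|---|---|---|
| 5% | -2.4 / +2.0 | -1.8 / +2.5 | -1.3 / +3.0 | -0.8 / +3.5 |
| 10% | -5.0 / +4.0 | -3.9 / +5.0 | -2.8 / +6.0 | -1.7 / +7.0 |
| 15% | -7.9 / +6.0 | -6.2 / +7.5 | -4.4 / +9.0 | -2.6 / +10.5 |
| 20% | -11.2 / +8.0 | -8.8 / +10.0 | -6.2 / +12.0 | -3.7 / +14.0 |

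With f = 0.5, the ranges over the same grid are -0.4 to -6.2 and +1.0 to +7.0. The extreme cell (20%, 40%) requires 0.77/0.80 = 96% suppression among returners, so it is an outer bound.

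**What this does to the decision.** Take the example with a true deficit of 9 points, so 76% in a fully traced home-delivery arm. If missing counts as not suppressed, control shows 80.0% and the apparent deficit is 4.0 points. If missing is excluded, control shows 88.9% and the apparent deficit is 12.9 points. With the same tracing in both arms, the expected artefact in this set-up is 0.

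**The case against.** The best defence is that the intervention itself creates the imbalance. Home-delivery participants receive ART from a CHW on what was their facility schedule, so they lose the routine reason to attend, while control participants still collect ART at the facility. Extra effort in the home-delivery arm then offsets a gap in completeness. This stands as a reason for tracing there, and for not cutting it back. It does not justify leaving control participants out. Those still in care will attend; those who have left care will not, and their home-delivery counterparts are sought. As worded, the rule also covers anyone in the home-delivery arm who has returned to facility care, which Data monitoring allows, but not a comparable control participant.

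The word 'only' is not in the text. The reading rests on the control arm being named neither in that sentence nor elsewhere. The Consent section's request to refusers will capture some control drop-outs, but not those who simply do not come.

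Three stronger readings are tempting and are not supported:
- *That the bias must run against home delivery.* This needs missing results to be excluded, which the article does not say. Its handling of missing exit values may be set in an analysis plan not shown, and its absence here is no fault.
- *That loss will be as heavy as the 39% in the Background section.* That figure is for the first 12 months after starting ART. Home-delivery eligibility requires at least six months on ART and evidence of stability, and home delivery lasts six months on average.
- *That a fixed number of home visits should be shared between arms.* Moving effort away from the arm where non-return is structurally expected could widen the gap in completeness.

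**Conclusion.** The point holds as a flaw in a stated procedure: the article names a bias condition that depends on both arms and applies its remedy to one. The sign of the artefact depends on a missing-data rule that the article does not give. In the central illustration it is -3.9 or +5.0 points, that is 3.9/9 = 43% or 5.0/9 = 56% of the margin. These figures rest on assumed non-return and assumed suppression among non-returners, and on complete tracing in one arm with none in the other. Half-successful tracing brings them to -2.0 or +2.5 points. Low non-return among control participants would make the artefact small. The size is therefore uncertain, but both the primary conclusion and its sensitivity to missing data would rest on ascertainment that differs by design.

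**What to change.** State one tracing rule, triggered by a missed exit assessment and not by arm. Every non-returner in both arms gets the same number of contact attempts, the same exit window and the same offer of a home blood draw. Do not reduce the effort planned for the home-delivery arm.

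Record how each exit viral load was obtained (facility or home) and report this by arm, together with the number still missing. Report a sensitivity analysis counting missing exit viral loads as not suppressed in both arms. It can be read at face value only once tracing is equal, since one-arm tracing shifts that analysis too.

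The cost is a modest number of extra home visits and blood draws for control non-returners, plus one analysis. The means already exist: the Enrolment procedure records the location of the home and telephone numbers and passes them to the CHW, and the Nutrition counseling section says "CHWs provide counseling to all participants in both the intervention and control arms during their home visits". The load is not nil. Enrolment blood is taken by the community outreach nurse, and most facilities have only one, so home draws around 24 further facilities need planning. Few control participants still in care should need them.
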